### Intervention

#### Treatment condition

The SCM is embedded in a multiprofessional network (see below) and consists of the following components:

### Diagnostic process and treatment selection

GPs of the intervention group continue the diagnostic process with a paper-pencil ICD-10-checklist to determine depression type and severity. Patients are given psycho-education about depression including evidence-based patient information. The decision about which evidence-based treatment option to carry out is made in cooperation with the patient (shared decision-making). Treatment interventions are allocated with consideration to depression severity and patient preference following guideline recommendations. The six treatment options (as well as the step 1 option of watchful waiting), the rationale for treatment selection within stratified stepped care and the care provider responsible for each treatment option are displayed in Table 1. While these recommendations offer a rationale orientation for treatment decisions, the assessment of the individual’s preferences may lead to different individual treatment decisions.

**Table 1 Tab1:** **Criteria for systematic treatment indication and description of responsible care providers for each step**

**Severity of the depressive disorder**	**Step in the SCM**	**Intervention**	**Responsible care provider**
Mild depressive disorder, duration: up to two weeks	1	Watchful waiting (active monitoring) for 2 weeks	GP
Mild depressive disorder, duration: over two weeks	2.a or 2.b	Bibliotherapy or Internet-based self-help program	GP
Mild to moderate depressive disorder, duration: over two weeks	2 plus	Telephone-based psychotherapy	Psychotherapist
Moderate depressive disorder	3.a or 3.b	Psychotherapy or pharmacotherapy	Psychotherapist or psychiatrist/GP
Severe depressive disorder without/ with suicidality	4	Combination therapy: psycho- and pharmacotherapy (inpatient or outpatient setting)	Psychotherapist and psychiatrist; clinic

### Step 2.a/2.b/2 plus

Three forms of low-intensity treatment for patients with mild depressive disorders are offered: 1) step 2.a: bibliotherapy; 2) step 2.b: the Internet-based self-management program “deprexis®” and 3) step 2 plus: telephone-based psychotherapy with a previous face-to-face contact conducted by a licensed psychotherapist.

In bibliotherapy, patients work independently and at their own pace with a cognitive-behavioral self-help book (“Selbsthilfe bei Depressionen”) [27], comprising detailed psycho-education and exercises with a focus on behavioral activation and cognitive restructuring. Personal guidance is limited in its scope and is carried out by the GP who gives an initial introduction to the intervention, hands out the book and monitors the progress of patients in this step.

In Internet-based self-management, the GP informs the patient about the program and the procedures and provides the patient with a personal license to register to the software. The program deprexis® is a certified medical product based on a cognitive-behavioral approach that allows patients to work independently and at their own pace [28]. The program consists of 12 interactive simulated conversations including detailed psycho-education and exercises. It focuses on behavioral activation and cognitive restructuring. For each patient, the program is tailored individually in terms of level of detail, language and personal relevance. The GP monitors and accompanies the patient during the three months scheduled to complete the program.

The telephone-based psychotherapy is the translated and adapted version of a specific intervention program [29–31] developed by researchers in Seattle. It includes a patient workbook as well as a therapist manual and will be evaluated in two conditions (delivery with vs. without additional motivating letters from the psychotherapist after each session). It comprises 8 to 12 telephone contacts (20 to 40 minutes) which are carried out weekly and - at a later treatment stage - biweekly. This 3-month structured program also follows a cognitive behavioral approach with the main focus on behavioral activation and cognitive restructuring. As the level of guidance and intensity in telephone-based psychotherapy is higher than in bibliotherapy and Internet-based self-management, it can also be carried out with patients suffering from moderate depression, especially if they decline step 3 (psychotherapeutic or pharmacological treatment).

### Step 3 and Step 4

Psychotherapy and/or pharmacotherapy (as stand-alone and as combination treatment) are conducted by health care providers in outpatient care (psychotherapy: psychologists or physicians licensed as psychotherapists; pharmacotherapy: psychiatrists or GPs) from routine care who undergo initial training and take part in four quality circles per year (see next section).

### Monitoring

Depression severity is systematically monitored by the responsible care provider within defined time intervals in order to ensure that a potential under- or oversupply is detected as quickly as possible. During monitoring patients fill out the PHQ-9 which is checked by the provider. Additionally, the care provider (GP, psychiatrist or psychotherapist) completes a monitoring sheet. This checklist assesses treatment-related information and is designed to facilitate decisions regarding further treatment (continuing current treatment, stepping up or down, treatment termination).

### Multiprofessional network

A necessary framework for the SCM is its integration in a network consisting of the relevant care providers involved in the treatment of depressive patients, i.e. GPs, psychotherapist, psychiatrists and inpatient care facilities. To build such a network these professional groups were sent information and personal invitations to join the project. Additionally, articles in professional journals advertising the study were published and professionals were contacted via telephone.

The main focus of the network is facilitation and enhancement of information exchange and communication between all network care providers of the network in order to increase the quality of patients’ health care. Another important aspect is the prompt referral to a secondary care provider like psychotherapist or psychiatrist. Information exchange about available treatment capacities in secondary care is enhanced using an online tool specifically developed for this project. Psychotherapists and psychiatrists indicate whether they currently have an available treatment capacity which implies that the psychiatrist or psychotherapist is able to offer the patient a first contact within the next three weeks. This way, GPs are able to make a reservation for their patients online and refer them into secondary treatment without delay.

### Training and quality standards

Previous to the implementation of the SCM, participating care providers obtain training regarding the recommendations of the German National Clinical Practice Guideline for unipolar depression [18], the rationale and the treatment concept of the SCM and the specific interventions. Each GP is additionally visited by the study team at least once in his or her practice to review the diagnostic routines in the everyday routine care. The psychotherapist for the telephone-based treatment receives special training and weekly supervision. Within the network, guideline-based quality standards are defined (e.g. type and frequency of monitoring). To ensure that these standards are met and to promote the cooperation and information exchange between the participating care providers, quarter-yearly quality circles take place. For the conception of the initial training and quality circles we could integrate experiences from former projects [32–35].

### Intervention for the control group

Patients in the control condition receive treatment as usual by their GP and within the regular German health care system. However, systematic screening with the risk-checklist, main-symptom-checklist and PHQ-9 are carried out in both intervention and control group to ensure a comparable recruitment and inclusion process.

### Outcome assessment

The main data collection comprises paper-pencil questionnaires which are filled out by the patients at four time points: The baseline questionnaire (t0) is handed out by the GP at intake and filled out before any treatment begins. The questionnaires 3 months (t1), 6 months (t2) and 12 months (t3) after baseline are sent to the patient’s by mail. For each completed questionnaire, patients receive an incentive of 5 €. Patients who fail to send back their questionnaires are reminded to do so twice by mail.

The *primary outcome parameter* for effectiveness is the change in depressive symptoms from baseline to t3 assessed by the PHQ-9. *Secondary outcome parameters* are response (defined as a 50% reduction in the PHQ-9 from t0 to t3) and remission (defined as < 5 points in the PHQ-9 at t3), change in health related quality of life (SF-12 and EQ-5D-3 L) and further clinical and psycho-social variables. To evaluate the cost-effectiveness of the SCM, direct and indirect costs as well as quality-adjusted life years (QALYs) based on the EQ-5D index are measured and the incremental cost-effectiveness ratio (ICER) is computed as further secondary outcomes.

Process analyses refer to treatment paths, decision processes and interface management. Additionally, feasibility and acceptance of the overall model of stepped care and of its components are analyzed taking patient and care provider perspectives into account. Table 2 summarizes the instruments for the patient self-ratings.

**Table 2 Tab2:** **Instruments and measurement points (patient self-ratings)**

	**Measurements**			
**Outcome variables**	**T0**	**T1**	**T2**	**T3**
Patient Health Questionnaire (PHQ-D)	X	X	X	X
Short Form Health Survey (SF-12)	X	X	X	X
EuroQol (EQ-5D-3 L)	X	X	X	X
General self-esteem scale (Rosenberg Self-Esteem-Scale RSES)	X	X	X	X
General self-efficacy scale (GSE)	X	X	X	X
Self-efficacy for management and relapse prevention in depression	X	X	X	X
Depression self-management behavior	X	X	X	X
Medical treatments and services received during the last 6 months	X	-	X	X
Medication during the last 6 months	X	-	X	X
Health care utilization during the last 3 resp. 6 months	-	X	X	X
Satisfaction with specific treatments during the last 3 resp. 6 months	-	X	X	X
Client Satisfaction Questionnaire (CSQ-8)	-	-	-	X
Helping Alliance Questionnaire (HAQ)	-	X	X	X
**Further (controlling) variables**	**T0**	**T1**	**T2**	**T3**
Sociodemographics	X	-	-	-
Social Support (F-Sozu-14)	X	-	-	-
Shared decision-making (SDM-Q-9)	X	-	-	-
Treatment motivation (FPTM-23, subscales “psychological burden” and “expectations”)	X	-	-	-
Former depression-specific treatments	X	-	-	-
Symptom course of depression	X	-	-	-
Referral procedures and interface management	-	X	X	X
Self-help experiences and habits	X	-	-	-

### Outcome instruments (patient ratings)

#### Patient Health Questionnaire (PHQ)

The German version [36,37] of the Patient Health Questionnaire [38] is used. Specific subscales assessing following syndromes were selected: major depressive syndrome (9 items), generalized anxiety syndrome (7 items), somatoform syndrome (13 items) and panic syndrome (11 items). Additionally, psychosocial functioning resp. psychosocial stressors are measured.

### Short Form Health Survey (SF-12)

The SF-12 assesses overall health-related quality of life and is based on the Short Form 36 Health Survey [39]. It is composed of the two subscales physical health and mental health. Scores are computed by calculating the sum of the 12 weighted items and then transforming it to a scale from 0 to 100, on which high scores indicate a high level of health-related quality of life.

### EQ-5D-3 L

This generic self-rating instrument measures health-related quality of life on five dimensions: mobility, self-care, usual activities, pain/discomfort and anxiety/depression [40,41]. Each dimension has three response categories that represent three levels of severity (“no problems”/“some or moderate problems”/“extreme problems”). Additionally, a visual analogue scale allows the general assessment of health-related quality of life. From the EQ-5D-3 L a preference-based index of health-related quality of life (EQ-5D index) can be derived [42].

### General self-esteem scale (revised version of the Rosenberg Self-Esteem-Scale)

The scale was originally designed by Rosenberg in 1965 to assess global self-esteem and translated to German [43]. It contains 5 positively and 5 negatively formulated items with statements referring to the subject’s global attitude towards him- or herself. The answers are given on a four-point scale. After recoding negative items a total score can be computed.

### General self-efficacy scale (GSE)

This self-rating instrument measures global optimistic beliefs about one’s self on a one-dimensional scale [44]. The underlying concept of self-efficacy includes the self-related expectation to be able to successfully cope with difficult situations. On ten items formulated as statements, subjects indicate their level of agreement on a four-point scale.

### Self-efficacy for managing and preventing depression

The depression-related self-efficacy is assessed on a ten-point scale, where subjects indicate the extent of trust in their own ability to cope with their depressive symptoms and complaints [45]. Psychometric analyses have confirmed the scale’s internal consistency.

### Depression-related self-management behavior

These five items cover depression-related self-management behavior to assess patients’ behavioral strategies for handling depression [46]. Patients are questioned about the frequency with which they integrate pleasant and social activities into everyday life as well as about their attention regarding depressive symptoms, early warning signs and situations which put them at risk of depressive episodes.

### Health care utilization during the last 3 resp. 6 months, satisfaction with specific treatments during the last 3 resp. 6 months

These two parts of the questionnaire aim to explore which offers patients made use of during the last 3 respectively 6 months and how they are perceived and evaluated.

### Client Satisfaction Questionnaire (CSQ-8) (German version ZUF-8)

On eight items, this questionnaire measures the extent of the patient’s satisfaction with received medical and psychotherapeutic treatment [47,48]. Important aspects are the interaction between care provider and patient, information about received treatment elements and the communication between the care providers.

### Helping Alliance Questionnaire (HAQ)

The German short version of this questionnaire consists of 11 items rated on a six-point scale [49]. The HAQ assesses the two factors “perceived helpfulness” and “collaboration or bonding”. It aims to capture the patient’s view of the relationship with the psychotherapist and of process variables. High scores indicate a high level of relationship quality.

### Additional control variables (patient-ratings)

#### Socio-demographic data

Following socio-demographic data is collected within a structured questionnaire: age, gender, nationality, family status, partnership, children, educational background, vocational training, housing and professional situation.

### Social Support (F-Sozu-14)

The 14-item Social Support questionnaire assesses perceived social support (practical and emotional support). By computing means, a total score from 1 to 5 points can be calculated [50].

### Shared decision-making (SDM-Q-9)

This instrument measures the extent to which the patient is involved in the decision-making process for the treatment [51]. It consists of nine items rated on a 6-point scale.

### Treatment motivation: specific subscales of the German Psychotherapy Motivation Questionnaire (Fragebogen für Psychotherapiemotivation FPTM-23)

To explore the different aspects of patients’ self-rated motivation for psychotherapeutic treatment the short version of this instrument with 23 items rated on a 4-point scale is employed [52].

### Further self-developed variables

Depression-specific treatments received prior to the study, medical treatments and services received during the last 6 months and medication during the last 6 months, symptom course of depression, referral procedures and interface management, self-help experience and habits.

### Additional instruments (health care provider ratings)

#### Documentation forms for screening, diagnostic and monitoring

These forms help to facilitate and support the diagnostic and treatment process (and are therefore elements of the intervention itself), as well as to document clinical processes for research purpose: They are used to analyze clinical treatment pathways and their quality as well as to draw conclusions about care providers’ adherence to the guidelines.

### Ratings on feasibility and acceptance

Each health care provider in the SCM fills out a questionnaire assessing the feasibility of and satisfaction and experiences with the SCM as a whole, the single components of the SCM (especially the innovative elements) and the quality of the multi-professional network.

### Structural information

Information regarding structural and organizational aspects of the primary care practices and the GPs are gathered in an interview at the beginning of the study. Issues covered are the size of the practices as well as their equipment, catchment area, workload and proportions of different work aspects (patient contacts, administrative tasks, etc.).

### Statistical analyses

The primary analysis of the change in depressive symptoms from baseline to t3 assessed by the PHQ-9 will be based on the ITT-population. In case of missing follow-up values, a last-observation carried forward (LOCF) imputation will be performed, that is, the baseline determination will be imputed as follow-up determination. A linear mixed model will be calculated with group (SCM/TAU) as a fixed effect and practice as a random effect under control of the baseline value of the PHQ-9 as covariate.

Only the result of this primary efficacy analysis will be interpreted in a confirmatory manner.

The secondary endpoints will be examined in an exploratory manner with appropriate procedures, including subgroup analysis of sex, socio-economic status and symptom severity of patients. Analyses of secondary endpoints should provide an indication on the consistency of the results from the evaluation of primary endpoints. The effects of the selected strata in the minimization algorithm on the primary and secondary endpoints will be evaluated additionally. Regression coefficients, 95% confidence intervals and p values will be reported. The analyses will be conducted with the newest SPSS version.

With regard to the assessment of cost-effectiveness direct and indirect costs will be calculated. Administrative and market prices will be used to value resource utilization. The human capital approach will be employed to value productivity losses. As effect measure QALYs will be calculated from the EQ-5D-3 L. The cost-effectiveness analysis will be performed from a societal perspective. As point estimate of cost-effectiveness the ICER (incremental costs per QALY) will be calculated. To assess the uncertainty of the results a cost-effectiveness-acceptability-curve (CEAC) based on non-parametric bootstrapping will be computed. A net-monetary benefit regression analysis will be performed.

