### Randomization

Cluster-randomization is performed in order to allocate confounding variables in equal parts to both study conditions and thus to control for potential bias in order to guarantee internal validity. In this study, cluster-randomization is undertaken at the level of the participating GP practices, which are allocated to either IG or CG in a 3:1 ratio. The process of randomization is conducted by a computer program by minimization based on the GP’s practice size (single practice vs. group practice), the location of the practice within Hamburg classified into the two categories (central vs. peripheral) and income level of the practice’s local district classified into three categories (low, middle and high). Criteria for selection of clustering variables are relevance and availability. We assume that each GP in the 49 participating practices is able to recruit 15–25 patients. A total of 36 practices is randomized into the IG and 13 practices into the CG.

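### The confirmatory mixed model omits the three minimisation factors, so its standard error is too large to the extent that those factors predict outcome (a minor, conservative inefficiency)

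*Protocol article*

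**What the plan says.** Under Randomization, the protocol article takes the GP practice as the unit, "which are allocated to either IG or CG in a 3:1 ratio". Allocation is "conducted by a computer program by minimization based on" practice size (single or group), location (central or peripheral) and income level of the local district (low, middle or high). The reason given for choosing these variables is short: "Criteria for selection of clustering variables are relevance and availability". The section counts 36 intervention and 13 control practices.

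Under Statistical analyses, the primary analysis is by intention to treat, and missing follow-up PHQ-9 values are replaced by the baseline value. The linear mixed model is specified "with group (SCM/TAU) as a fixed effect and practice as a random effect under control of the baseline value of the PHQ-9 as covariate". The article reserves confirmatory interpretation for this one analysis. The minimisation factors appear only in the later paragraph on exploratory work: "The effects of the selected strata in the minimization algorithm on the primary and secondary endpoints will be evaluated additionally".

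The article therefore lists the terms of the primary model and places the factors outside it. It does not leave the choice open for a later document.

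**The concern.** Minimisation restricts how far the arms can differ on the chosen factors. Whatever those factors contribute to outcome is then largely cancelled in the difference between arms. A model without them does not know this. It sees practices that differ in outcome, partly because of size, location or district income, and counts all of that spread as random between-practice variation. The random practice effect is no remedy, because the factors are themselves practice-level and their variance sits inside that term.

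Three things follow if the factors are prognostic: a confidence interval that is too wide, a test that rejects less than 5% of the time under the null, and some loss of power. An adjusted result produced only as an additional analysis cannot take over the confirmatory role, because the article gives that role to a single model. If the two models disagreed, the less suitable one would decide.

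**Working it through.** **Reproducing the plan's own figures.** Inputs from Sample size and power calculation: d = 0.4, two-sided α = 0.05, power 80%, ICC 0.05, 20 patients per practice.
- The t-based solution is 99.1 per group; the article gives 100.
- Design effect = 1 + (20 − 1) × 0.05 = 1.95, as stated.
- 100 × 1.95 = 195, which the article rounds up to 200.

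**Model standard error on the intention-to-treat set.** Inputs: 660 patients in 36 practices and 200 in 13. The SD is set to 1 and practices are taken as equal in size within arm.

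SE² = [1 + (m₁ − 1)ρ]/660 + [1 + (m₀ − 1)ρ]/200, with m₁ = 660/36 = 18.33 and m₀ = 200/13 = 15.38.
- ρ = 0.05: 1.867/660 + 1.719/200 = 0.01142, SE = 0.1069.
- ρ = 0.04 (20% of between-practice variance explained): SE = 0.1022, or 4.4% smaller.
- ρ = 0.03 (40% explained): SE = 0.0973, or 9.0% smaller.

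The 20-40% is an assumption; the documents give no figure. As a cross-check, the between-practice part is 0.05 × (1/36 + 1/13) = 0.0052, about 46% of the total 0.0114. Subtracting 20-40% of that part directly, with the within-practice variance unchanged, shrinks the SE by about 5-10%. The two calculations agree closely.

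**What this does to the test.** The formula gives only the SE that each model reports. To see error rates, 3:1 minimisation of 49 practices was simulated with 860/49 = 17.55 patients each and ICC 0.05, using 4,000 runs per scenario. Practice means were analysed with and without the factors, which with equal practice sizes is equivalent to the random-practice model. The simulation also assumes equally frequent factor levels, equal contributions from the three factors, a biased-coin rule and no dilution of d by imputation.

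| Between-practice variance explained | Reported SE too large by (no factors) | Type I error without / with | Power at d = 0.25, without / with | Power at d = 0.4, without / with |
|---|---|---|---|---|
| 0% | about 0% | 4.8 / 5.1% | 62.6 / 62.7% | 95.5 / 95.4% |
| 10% | 2-4% | 4.6 / 5.1% | 63.5 / 64.4% | 96.1 / 96.3% |
| 25% | 4-8% | 3.9 / 4.8% | 64.3 / 68.3% | 96.6 / 97.3% |
| 50% | 14-15% | 2.8 / 4.8% | 64.8 / 75.0% | 97.4 / 98.8% |

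Simulation error on a 5% rate is √(0.05 × 0.95/4000) = 0.34 points. The 4.6% at 10% explained is therefore within noise of 5%, while 3.9% and 2.8% are not.

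The true spread of the estimate hardly differs between the two models: SD 0.1005 without and 0.1004 with the factors at 25% explained, and 0.0937 and 0.0929 at 50%. Minimisation has already secured most of the gain in the estimate. What the unadjusted model gets wrong is the reported SE.

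**Cost when the factors explain nothing.** SE 0.107 with them against 0.106 without. The residual practice-level degrees of freedom go from 49 − 2 = 47 to 43.

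**The case against.** The case for leaving the model alone is reasonable. It is pre-specified. Its error is on the safe side, so a significant result stands. The harm depends on a quantity that the documents do not give, and the baseline PHQ-9 covariate may absorb part of any district-income effect. The article also commits in advance to examining the factors on the primary endpoint. All of this stands, and it limits how heavily the point can weigh. The additional analysis is only partial mitigation: the article does not say whether it estimates an adjusted group effect, and its result could not be confirmatory in any case.

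Three stronger readings are tempting, and the documents do not support them.
- *The trial loses scarce power at its planned effect.* A calculation on completers (660 × 0.8 = 528 and 200 × 0.5 = 100) gives SE 0.1286 and 87.5% power, rising to 91.0% at 40% explained. However, the primary analysis is intention to treat with imputation, so all 860 patients enter and power by the same formula starts at about 96%. The comparison also gives the unadjusted model too little power, because under minimisation its estimate varies less than its reported SE suggests.
- *The standard error is certainly too large.* The article says only that the factors were chosen for relevance and availability. If they explain nothing, nothing is lost.
- *Residual imbalance among the 13 control practices biases the result.* Some imbalance can remain, but it causes no bias in expectation. In the simulation it added almost nothing to the spread of the estimate.

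**Conclusion.** The mismatch between allocation and confirmatory analysis is in the text. Its consequence is conditional and modest. To the extent that the factors are prognostic, the primary model overstates its standard error and tests below 5%. With 20-40% of between-practice variance explained, including the factors lowers the model SE by about 4-9%. The simulated scenarios on either side of that range put type I error without them between 4.6% (10% explained) and 2.8% (50%), against about 5% with them. At d = 0.4 the power gain is about one point; at d = 0.25 with 25% explained it is about four points (64% to 68%).

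These sizes rest on the article's ICC of 0.05, the assumed explained share, and a d not altered by carrying baseline values forward. With expected drop-out of about 20% and 50% in the two arms, the effect actually tested may differ from 0.4. This is a minor improvement available at almost no cost. It is not an error that threatens the validity of the trial.

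**What to change.** In Statistical analyses, add practice size (single/group), location (central/peripheral) and district income (low/middle/high) as fixed effects to the primary mixed model, next to group, random practice and baseline PHQ-9. Report the model without the three factors as a sensitivity analysis, and fix this before outcome data are seen. If a separate statistical analysis plan already includes the factors, the two documents need to state the same primary model.

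The cost is one sentence and four parameters (1 + 1 + 2). The variables are already held from allocation. If the factors prove irrelevant, the penalty is four of about 47 practice-level degrees of freedom and a negligible change in the standard error.
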